**Exclusion criteria**
Participants will be excluded if they meet any of the following conditions:Compromised circulation, injury, or physical abnormalities affecting fingers, hands, ears, forehead/skull, or other regions of interest essential for study testing.The presence of tattoos in the optical path hinders the assessment of necessary regions of interest.Severe allergies to standard adhesives, latex, or other materials used in medical sensors for measuring vital signs.Medical conditions that, in the investigator’s opinion, prevent the conduct of study assessments.Considered unfit for participation by the investigator.

Additional inclusion criteria.Prediabetes or diabetes with glycated hemoglobin (HbA_1c_) levels between 5.7% and 13%:30% of participants with HbA_1c_ 5.7%-6.4%.30% of participants with HbA_1c_ >6.4%.Hypertension with systolic measurements exceeding 130 mm Hg:40% of participants with systolic blood pressure >130 mm Hg.20% of participants with systolic blood pressure >160 mm Hg.Total cholesterol:40% of participants with levels >200 mg/dL and/or low-density lipoprotein cholesterol >130 mg/dL.Atrial fibrillation (~1% prevalence).Smokers, constituting approximately 20%-30% of the study cohort.

Procedures and evaluations.Obtain participant consent and, if agreed, additional consent for a blood sample.Review eligibility: assess eligibility as described in the inclusion and exclusion criteria.Record the participants’ medical and medication history: each medical problem encountered is classified into the sector of the body involved and for each of these, the starting date and the drugs used for treatment are indicated.Record participant demographics, including date of birth, age, smoking, and alcohol drinking habits.Record body characteristics including height, weight (BMI will be calculated as a person’s weight in kilograms divided by the square of height in meters), and skin tone using the Fitzpatrick scaleInterview the patient about his feelings in the last 2 weeks and if he has suffered from problems such as anxiety, nervousness, lack of control, loss of interest in doing things, or depression.

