**Figure 3 figure3:**
[figure not shown]
Measurement procedure flow.

The “by face” method for remote photoplethysmography vital signs data collection involves recording participants’ faces using the front camera of mobile devices (iOS and Android) for approximately 1.5 minutes.

During “by face” data collection, participants will be seated comfortably, facing a screen at approximately 25 cm, with their faces fully visible (without wearing masks, hats, or any facial accessories). Participants are required to maintain stable breathing and minimal movement and to gaze directly at the camera throughout the data collection process.

Simultaneously, vital signs data (SpO_2_, RR, BP, and PR) will be continuously collected for about 1.5 minutes using the reference devices alongside data collected via the Comestai app.

BP measurements will be taken using the reference devices before and immediately after data collection with the Comestai app.

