### Statistical Analysis

Numerical variables will be presented as minimum and maximum values, means, SDs, medians, and quartiles. Categorical variables will be presented as absolute and relative frequencies.

The accuracy of the app measurements compared to the reference devices and standard tests will be assessed for all parameters. CIs will be calculated using the bootstrap method. Participants with abnormal adverse events (defined as 3 SDs or more above the mean) and those with invalid reference device values will be excluded from the analysis.

In order to provide a more comprehensive view of the model’s performance, the proposed approach’s effectiveness was evaluated using various quality criteria, including the mean error, SD, mean absolute error, root mean square error, and mean absolute percentage error. The correlation between measurements obtained using the app and those from reference devices and standard tests will be evaluated using the Pearson correlation coefficient. The agreement between the 2 sets of measurements (app vs reference devices/standard tests) will be represented using Bland-Altman plots. Sensitivity, specificity, positive predictive value, negative predictive value, accuracy, and likelihood ratios will be calculated to determine the ability of the new app to accurately measure vital signs.

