### Sample Size Estimation

Considering the average values of pressure/saturation/HR among a general population with a sample of 3000 participants, there will be a power exceeding 95% for all evaluated parameters in a 2-sided test with a *P* value of .05 if the discrepancy between the 2 measurement methods is as reported in Table 2.

**Table 2 table2:** Expected error level of the measurements.

Vital	Range	Unit of measurement	Error level
Pulse rate	50-180	BPM^a^	RMSE^b^ ≤3
Respiratory rate	8-30	BrPM^c^	RMSE ≤3
Blood pressure systolic	80-180	mm Hg	MAE^d^ ≤15
Blood pressure diastolic	50-120	mm Hg	MAE ≤10

^a^BPM: beats per minute.

^b^RMSE: root mean square error.

^c^BrPM: breaths per minute.

^d^MAE: mean absolute error.

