### Strengths and Limitations

Today’s health care industry embraces technological innovations to provide better personalized health care services to the public [17]. Mobile-based solutions and apps are one such revolutionary and trending innovation that facilitates enhanced patient care management and efficient diagnosis. They are increasingly reliant on wireless technologies as they evolve [17]. Applications of mHealth typically include the use of mobile devices in the collection of health and clinical data, the provision of health information to practitioners, researchers, and patients, the real-time monitoring of patients; vital signs, and the direct delivery of care (via mobile telemedicine).

In an mHealth context, the advancement of noncontact methods to monitor human vital signs holds substantial promise for enhancing patient care across various environments [6].

A recently proposed RGB camera–based method for noncontact vital sign measurement using photoplethysmography has been identified as an interesting tool for recording vital signs. Photoplethysmography is also used by the Comestai app to assess various vital functions, including SpO_2_, RR, BP, and PR [10]. Initial research into photoplethysmography shows promising outcomes; however, scientific evidence regarding the accuracy and benefits of digital health apps that measure vital signs remains limited and somewhat controversial. Many photoplethysmography studies are still susceptible to errors [18-20], with the majority involving only small sample sizes.

In our protocol, we will recruit a large population (3000 participants) to ensure accuracy across various demographics and health conditions, including also pathological conditions. The use of a large population will also help reduce errors in the results, improving the reliability of the tool. Thorough analysis and classification of these signals are essential for the development of affordable and user-friendly PPG-based tools across a wide range of applications [10].

While there is an increasing number of articles and research on SpO_2_, RR, BP, and PR monitoring using PPG, a limited number of available publications on advancements related to biochemical parameter estimation are reported [10]. Comestai offers the possibility to monitor Hb, HbA_1c,_ and cholesterol concurrently with other parameters, thereby broadening its application possibilities in health care services.

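### Table 2's single pooled error level per vital sign is too loose to support accuracy across health conditions, and its upper pulse and respiratory ranges will be almost empty

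*Protocol article*

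**What the plan says.** The Statistical Analysis section evaluates the app by aggregate measures, "including the mean error, SD, mean absolute error, root mean square error, and mean absolute percentage error", together with Pearson correlation, Bland-Altman plots, and sensitivity, specificity, predictive values and likelihood ratios. No acceptance value, cut-off or stratum is attached to any of them there.

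Numerical levels appear only under Sample Size Estimation. Power is claimed to exceed 95% "if the discrepancy between the 2 measurement methods is as reported in Table 2". That table, titled "Expected error level of the measurements", gives one level per vital sign:

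- pulse rate, RMSE at most 3 over 50-180
- respiratory rate, RMSE at most 3 over 8-30
- systolic pressure, MAE at most 15 over 80-180
- diastolic pressure, MAE at most 10 over 50-120

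The Introduction says the results will show whether the app is accurate enough to be adopted for self-monitoring and for detecting early deterioration. Strengths and Limitations says "we will recruit a large population (3000 participants) to ensure accuracy across various demographics and health conditions". The additional inclusion criteria set quotas such as "40% of participants with systolic blood pressure >130 mm Hg" and a further 20% above 160 mm Hg. Fitzpatrick skin type is recorded without a quota. Atrial fibrillation is expected at about 1%. Readings follow 2 minutes of seated stabilization, and "Participants are required to maintain stable breathing and minimal movement".

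**The concern.** A pooled MAE or RMSE is a weighted average over everyone measured. If most participants have ordinary values, the average can look acceptable while the app is badly wrong in the minority whose values matter for screening. The levels are also wide relative to the ordinary spread between people, so for some vital signs an app carrying little information could meet them.

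The tabulated ranges extend to values that resting participants rarely show, and no quota brings in fast or slow rates. At stake is the final claim. A statement that the error levels were met would be read as accuracy in hypertension, in all skin tones and over the printed ranges, when the pooled figure supports none of these.

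**Working it through.** **The plan's own figure.** The claim of more than 95% power cannot be reproduced, because neither a standard deviation nor a null hypothesis is given. A paired test of a mean difference as large as the Table 2 level has power of about 1.00 at N = 3000 for every SD tried. With an SD of differences of 18.8, the mean difference detectable with 95% power is (1.96 + 1.645) × 18.8/√3000 = 1.24 mm Hg. The claim is therefore plausible for a mean difference, but it says nothing about error within a stratum.

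**1. What pooling allows, with no distribution assumed.** With stratum shares w, pooled MAE = Σ w × MAE and pooled RMSE² = Σ w × RMSE².

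- Systolic, 20% above 160, MAE 10 in the rest: (15 − 0.8 × 10)/0.2 = 35 mm Hg at a pooled 15.
- If the 20% applies only to the enriched 70% of the sample, the share is 14%: (15 − 0.86 × 10)/0.14 = 45.7 mm Hg.
- Pulse, RMSE 2 in the rest, for a skin-tone group with an *assumed* share of 5%: √((9 − 0.95 × 4)/0.05) = 10.2 bpm at a pooled 3. With shares of 10% and 20% the figures are 7.3 and 5.4.

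**2. A concrete systolic example.** The quotas are read as 60% up to 130, 20% from 130 to 160 and 20% above 160. The assumed shapes are a normal (118, SD 10) truncated at 130, a uniform, and 160 plus an exponential with mean 8. The simulated mean is 132.1 and the SD 22.8. The app reading is 132.1 + 0.3 × (true − 132.1) + noise with SD 5.

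| Band | Share | Mean error | MAE |
|---|---|---|---|
| up to 130 | 60% | +11.4 | 11.7 |
| 130-160 | 20% | −9.0 | 10.0 |
| above 160 | 20% | −25.1 | 25.1 |
| pooled | 100% | 0.0 | 14.1 |

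Pooled check: 0.6 × 11.7 + 0.2 × 10.0 + 0.2 × 25.1 = 14.0, which agrees with 14.1 apart from rounding. The correlation is 0.81. Four readings of the quotas (shares of everyone, of the 70%, of hypertensives, or 40% and 20% as separate groups) were also tried with other assumed shapes. Slopes of 0.25 to 0.5 gave pooled MAE 8.7 to 14.6 and mean error above 160 of −15 to −36 mm Hg.

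**3. A constant reading.** For a normal variable, a constant at the mean has MAE = 0.798 × SD and RMSE = SD.

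- Diastolic level met if SD ≤ 10/0.798 = 12.5.
- Respiratory level met if SD ≤ 3.
- Systolic would need SD ≤ 15/0.798 = 18.8. In the quota sample above, the constant's MAE is 19.6, so it *fails*. It also fails under the other quota readings (15.5 to 18.5).

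**4. Who will populate the ranges.** For normal resting values (assumed), the expected number above c is 3000 × P(Z > (c − mean)/SD).

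| Assumed pulse mean, SD | above 100 | above 120 |
|---|---|---|
| 70, 10 | 4 | 0 |
| 72, 11 | 16 | 0 |
| 75, 12 | 56 | 0.3 |

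For respiratory rate with mean 15-17 and SD 2.5-4, 68 to 680 exceed 20, 0 to 68 exceed 25 and 0 to 9 exceed 28. If 20 people exceed 100 bpm and the rest have RMSE 2, those 20 could have RMSE √((3000 × 9 − 2980 × 4)/20) = 27.5 bpm at a pooled 3.

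**The case against.** Four points on the other side have force.

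- **Table 2 is not written as a pass/fail rule.** It states expected error in the sample-size section. A reader might infer that the trial will declare success when the pooled levels are met, but the article does not say so. What remains is that no other number defines adequate accuracy.
- **Other planned analyses would expose the example app.** Its Bland-Altman slope is about −1, its limits of agreement are about ±33 mm Hg, and its sensitivity above 160 is roughly 0.2%. A reader might infer that every planned metric hides the failure, which is not so. However, no criterion or cut-off is attached to these analyses. At 130 mm Hg the same app has sensitivity 92% and specificity 69%, so what is seen depends on an unstated cut-off.
- **Stratified tables may be in an analysis plan that is not shown.** Their absence from a journal article is no fault. The point rests on the levels and ranges the article does fix, set against the aim it states.
- **Several inputs are assumptions.** These are the skin-tone share, the resting rate distributions and the shape of systolic pressure. The documents do not support saying that the app fails in dark skin; they only show that the pooled level would not reveal it. High systolic pressure is sampled by quota, so scarcity of cases is a pulse and respiratory problem. Strengths and Limitations also concedes that the controlled setting is a limitation.

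**Conclusion.** The point holds in this form: the article's only numerical accuracy levels are pooled and loose, and they cannot support a claim of accuracy across demographics and health conditions. The mixture result is arithmetic: MAE 35 mm Hg above 160 is compatible with a pooled 15 when 20% of all participants are in that band and the rest have MAE 10. The quota denominator is unclear, but the conclusion survived every reading tried.

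A stronger reading, that an app with no information would meet Table 2 throughout, is not supported. It is possible for diastolic pressure (SD 12.5 or less) and respiratory rate (SD 3 or less), but not for systolic pressure under these quotas. The near-empty upper ranges follow from resting measurement without a rate quota; the exact counts depend on the assumed distributions. This is a worthwhile, inexpensive improvement to the analysis and to the wording of the claim, and does not make the study invalid.

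**What to change.** 1. Report each Table 2 metric with its bootstrap confidence interval, pooled and within systolic bands (up to 130, 130-160, above 160 mm Hg) and Fitzpatrick groups. Keep atrial fibrillation, about 30 people, descriptive only.
2. Beside each value, print the result for a no-information predictor (the sample mean) and the slope of difference on reference. Error in the reference itself produces some negative slope, so read it with the Bland-Altman plot.
3. Limit the accuracy statement to strata and value ranges that hold a prespecified minimum count and in which the level is met.
4. Restate the Table 2 ranges as those actually observed.
5. State the denominator of the systolic quotas.

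The cost is a few extra tables from data already being collected. Confidence intervals will be wide in small strata, and the final claim will be narrower.

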**Methods:**

A total of 3000 participants will be consecutively enrolled to achieve the objectives of this study. In all patients, personal data, medical condition, and treatment overview will be recorded. The “by face” method for remote photoplethysmography vital sign data collection involves recording participants’ faces using the front camera of a mobile device (iOS or Android) for approximately 1.5 minutes. Simultaneously, vital signs will be continuously collected for about 1.5 minutes using the reference devices alongside data collected via the Comestai app; biochemical results will also be recorded. The accuracy of the app measurements compared to the reference devices and standard tests will be assessed for all parameters. CIs will be calculated using the bootstrap method. The proposed approach’s effectiveness will be evaluated using various quality criteria, including the mean error, SD, mean absolute error, root mean square error, and mean absolute percentage error. The correlation between measurements obtained using the app and reference devices and standard tests will be evaluated using the Pearson correlation coefficient. Agreement between pairs of measurements (app vs reference devices and standard tests) will be represented using Bland-Altman plots. Sensitivity, specificity, positive predictive value, negative predictive value, accuracy, and likelihood ratios will be calculated to determine the ability of the new app to accurately measure vital signs.

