## Methods

### Recruitment

The objectives of this study will be achieved by recruiting 3000 participants from the outpatient clinic of ASST-Fatebenefratelli-Sacco, Buzzi Children’s Hospital, and IRCCS MultiMedica in Milan, Italy. All participants who meet the inclusion criteria and provide consent to participate will be enrolled consecutively. Recruitment will take place from June 2024 to September 2025.

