### Eligibility Criteria

Participants eligible for inclusion in the study must meet the criteria in Textbox 1.

In addition to the above criteria, 70% of the target population should include adult participants meeting at least one of the conditions in Textbox 2. Family history of diabetes or hypertension will also be investigated.

The procedures and evaluations in Textbox 3 will be performed during screening to enroll eligible participants.

Characterizing aspects will be noted, such as scars, piercings, beards, glasses, or the use of facial products, sunscreen cream, or nail polish. Furthermore, current pregnancy will be reported.

The flowchart of the process is schematized in Figure 1.

Inclusion and exclusion criteria.

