## Discussion

### Principal Findings

The project aims to report whether this user-friendly mobile app supports a high level of accuracy in monitoring SpO_2_, RR, BP, and PR, demonstrating the same reliability in detecting Hb, HbA_1c_, and total cholesterol. Enhancing algorithm performance and achieving a high level of accuracy will be crucial in assessing whether the app can be adopted to improve self-monitoring of health status. This, in turn, could enhance the screening for early abnormalities in vital signs and biochemical parameters.

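### Quota-set disease frequencies conflict with consecutive enrolment, and crude PPV, NPV and Pearson r from the enriched sample will not carry over to a screening population

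*Protocol article*

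**What the plan says.** **Sampling.** The abstract's Methods paragraph states "A total of 3000 participants will be consecutively enrolled to achieve the objectives of this study", and the Recruitment section repeats the idea: "All participants who meet the inclusion criteria and provide consent to participate will be enrolled consecutively". The Eligibility Criteria section then adds that "70% of the target population should include adult participants meeting at least one of the conditions in Textbox 2". Textbox 2 sets individual shares, among them "30% of participants with HbA_1c_ 5.7%-6.4" and "30% of participants with HbA_1c_ >6.4" (HbA1c, both in per cent), 40% with SBP above 130 mm Hg, "20% of participants with systolic blood pressure >160 mm Hg", and 40% with raised total or LDL cholesterol. It also lists atrial fibrillation at about 1% and smokers at 20-30%. The base of these percentages is not given.

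**Analysis.** The Statistical Analysis section says "Sensitivity, specificity, positive predictive value, negative predictive value, accuracy, and likelihood ratios will be calculated" in order to judge how accurately the app measures vital signs. It also plans the Pearson correlation, Bland-Altman plots, mean error, SD, MAE, RMSE and MAPE.

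**Use.** The abstract's Conclusions and the Future Research section present such apps as screening tools. On better accuracy, Principal Findings says "This, in turn, could enhance the screening for early abnormalities in vital signs and biochemical parameters".

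**The concern.** Two stated choices do not fit together. Enrolling everyone who is eligible and consents lets the case mix fall where it may. Preset shares require targeted recruitment or passing people over once a group is full. The article says both and does not explain how they combine.

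This matters because PPV and NPV depend on the share of cases in the sample, and here that share is a design decision. Pearson r depends on the spread of the reference values, which oversampling of high SBP widens. A reader who is told that the sample is consecutive, that the sample size rests on average values in a general population, and that the purpose is screening could take a crude PPV as the app's performance in use. The Strengths and Limitations section names the controlled setting as a limitation but not the enrichment.

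**Working it through.** The article states no prevalence, predictive value or correlation, so there is no figure of its own to reproduce on this point. The power statement under Sample Size Estimation does not bear on it.

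**Inputs from the article.** 3000 participants; the 70% share; the Textbox 2 shares; SBP error level MAE ≤15 mm Hg (Table 2).

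**Assumptions.** Sensitivity (se) and specificity (sp) of 0.80, varied below; a cut-off at 130 mm Hg, taken from Textbox 2; the group above 160 mm Hg nested in the group above 130; target prevalences of 20% and 10%.

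**Step 1: the denominator.** If the base is 3000, the shares stand as printed. If it is the 70%, SBP above 130 is 0.70 × 40% = 28% of all participants, SBP above 160 is 0.70 × 20% = 14%, cholesterol is 28%, and HbA1c of 5.7% or more is 0.70 × 60% = 42%.

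**Step 2: predictive values.** With prevalence p:

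- PPV = se·p / [se·p + (1 − sp)(1 − p)]
- NPV = sp(1 − p) / [sp(1 − p) + (1 − se)p]

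At p = 0.40 and se = sp = 0.80, PPV = 0.32 / (0.32 + 0.12) = 0.727 and NPV = 0.48 / (0.48 + 0.08) = 0.857. Likewise:

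| Prevalence | PPV (0.80) | NPV (0.80) | PPV (0.90) | NPV (0.90) |
|---|---|---|---|---|
| 60% (HbA1c, base 3000) | 0.857 | 0.727 | 0.931 | 0.857 |
| 42% (HbA1c, base the 70%) | 0.743 | 0.847 | 0.867 | 0.926 |
| 40% (SBP >130 or cholesterol, base 3000) | 0.727 | 0.857 | 0.857 | 0.931 |
| 28% (the same, base the 70%) | 0.609 | 0.911 | 0.778 | 0.959 |
| 20% | 0.500 | 0.941 | 0.692 | 0.973 |
| 10% | 0.308 | 0.973 | 0.500 | 0.988 |

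**Step 3: overall accuracy.** Accuracy = se·p + sp(1 − p). With se = sp it does not move with p. With se 0.7 and sp 0.9 it is 0.88 at 10% and 0.82 at 40%; with se 0.9 and sp 0.7 it is 0.72 and 0.78. It has no fixed direction.

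**Step 4: Pearson r for SBP.** If errors are normal with mean 0 (assumption), an MAE of 15 gives an error SD of 15 × √(π/2) = 18.8 mm Hg. Then r = SD_ref / √(SD_ref² + 18.8²). For an assumed unenriched SD of 12 to 18 mm Hg, r is 0.54 to 0.69. To impose the quotas, I simulated normal SBP with mean/SD of 120/12, 125/15 and 130/18, with values above 160 spread evenly up to 180. The SD becomes 22.6 to 23.4 and r 0.77 to 0.78 (base 3000), or 20.7 to 21.7 and 0.74 to 0.76 (base the 70%). The app error is the same throughout.

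**Step 5: severity mix and direction.** The same simulation, cut at 130 mm Hg, with the quotas on base 3000:

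| Unenriched SBP (share >130) | Sensitivity | PPV | NPV |
|---|---|---|---|
| 120/12 (20%) | 0.633 → 0.807 | 0.390 → 0.684 | 0.890 → 0.854 |
| 125/15 (37%) | 0.691 → 0.832 | 0.612 → 0.682 | 0.803 → 0.869 |
| 130/18 (50%) | 0.744 → 0.850 | 0.743 → 0.686 | 0.744 → 0.881 |

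Specificity stays between 0.74 and 0.75. Oversampling SBP above 160 raises sensitivity as well. In the third row, where the unenriched share already exceeds the quota, PPV falls instead of rising.

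**The case against.** The case on the other side is substantial, and several parts of it stand.

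- **Scope.** The classification sentence concerns vital signs, and among these only SBP has a quota. Pulse rate, respiratory rate and SpO2 have none, nor does Hb. The 60% figures apply to HbA1c, and only if the same measures are used for it. This stands.
- **A uniform overstatement.** A reader might infer that the sample flatters every measure. It does not: at fixed sensitivity and specificity enrichment lowers NPV, and accuracy can move either way or not at all.
- **A PPV that is seriously too high.** This is also tempting, but recruitment is from hospital outpatients and no target prevalence is given. The third row of the simulation shows that the direction can reverse.
- **Arithmetic conflict with the 70%.** If the conditions were independent, 1 − 0.4 × 0.6 × 0.6 = 86% would have raised HbA1c, SBP or cholesterol, which might seem to contradict 70%. Independence is not stated. With full overlap these three groups cover 60%, so 70% is attainable.
- **Existing safeguards.** Sensitivity, specificity, likelihood ratios, error measures and Bland-Altman plots are already planned. The expected error levels are RMSE and MAE, and r is assigned to correlation, not agreement.
- **Disclosure.** The enrichment is published, and Strengths and Limitations explains that diseased participants were included to test pathological values. Some shares are worded as approximate, and consecutive enrolment within strata would be possible, although the article does not say so.

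None of this reconciles the two descriptions of sampling or supplies the denominator. Nor does it turn a crude PPV from a preset case mix into an estimate for screening.

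**Conclusion.** The point holds in a bounded form. Consecutive enrolment and preset case shares are both stated and must be reconciled, and the base of the shares is open. Crude PPV and NPV will reflect the quota mix. For SBP above 130 mm Hg, with sensitivity and specificity assumed at 0.80, PPV in the sample would be 0.73 or 0.61 depending on the base, against 0.50 and 0.31 at prevalences of 20% and 10%. NPV would be 0.86 or 0.91, against 0.94 and 0.97. So relative to a lower-prevalence population PPV is too high and NPV too low at fixed sensitivity and specificity. Pearson r also rises with the widened range at unchanged app error.

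This applies directly to SBP, and to HbA1c and cholesterol if the same measures are used for them. Sensitivity, specificity, SBP spread and target prevalence are all assumptions here, and both size and direction turn on the target prevalence. The part on r is minor because better agreement measures are already planned. The change should be made, but the point does not put the planned error measures in doubt.

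**What to change.** 1. Reconcile the wording in the abstract and Recruitment with Eligibility Criteria and Textbox 2: describe the design as quota or enriched sampling, and state whether the percentages are of 3000 or of the 70%.
2. Make sensitivity, specificity and likelihood ratios the main classification measures. Report them by severity stratum (for SBP, separating values above 160 mm Hg), because the severity mix can itself raise sensitivity.
3. Give PPV and NPV as projections over stated target prevalences, using the formulas above. Label any crude PPV, NPV or accuracy as specific to the enriched sample.
4. Rest agreement on the bias, Bland-Altman limits and RMSE/MAE already planned, with r descriptive only.

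The cost is slightly more analysis text, and PPV figures that may look less favourable. No further participants or measurements are needed.
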